## Treatment of Patients

### Staging

Diagnostic workup includes an upper GI endoscopy with the description of the tumor location and a biopsy for histology. Clinical staging is assessed through the execution of contrast-enhanced computed tomography (CT) scan. On CT scan, suspected LNs are defined as LNs with short-axis diameter >5 and >8 mm in the case of perigastric and extraperigastric nodes, respectively (36). Endoscopic ultrasound (EUS), F-fluorodeoxyglucose (FDG) positron emission tomography (PET)/CT, and staging laparoscopy can also be performed at the discretion of the attending surgical team/tumor board. Preoperative/pretreatment clinical stage is defined according to the eighth edition of the UICC Staging System (TNM) (10).

### Neoadjuvant Chemotherapy

The indication to neoadjuvant chemotherapy (NACT) is evaluated for every patient by the local multidisciplinary tumor board according to national and international guidelines (4, 36). NACT is defined as any chemotherapy received within 8 weeks before surgery.

### Restaging

Restaging is performed after NACT with total body CT scan performed within 4 weeks after completion of NACT in order to rule out progressive disease (PD) or distant metastasis and confirm surgical indication. In the absence of PD or distant metastasis, curative treatment surgery is performed within 6 weeks after NACT completion.

### Step 1: Endoscopic ICG Injection

The steps of the iGreenGO Study are graphically summarized in **Figure 1**.

**Figure 1 f1:**
[figure not shown]
Summary steps of the iGreenGO study. NIR/ICG, near-infrared/indocyanine green.

Patients undergo upper GI endoscopy at any time between 20 h before and the initiation (skin incision) of the planned surgery. The ICG powder (Verdye**
^®^
** 5 mg/ml, 25 mg powder for solution for injection, Diagnostic Green, Aschheim-Dornach, Germany) is dissolved in sterile water, obtaining a final concentration of 0.125 mg/ml. Two milliliters of the obtained solution is injected in the submucosa with a 23-gauge endoscopic needle (introduced through the flexible scope working channel) into four peritumoral sites, 0.5 ml for each site. In the case of stenotic cancers, ICG injection can be performed at four proximal tumor points.

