**Methods:**

This is the protocol of the “iGreenGO” (indocyanine Green Gastric Observation) Study, a national prospective multicenter study. Western patients who undergo curative-intent gastrectomy with D2 lymphadenectomy for AGC constitute the study cohort. All the patients undergo preoperative upper gastrointestinal endoscopy for submucosal peritumoral ICG injection at the most 20 h before surgery. Intraoperative endoscopic injection before starting surgical dissection is also allowed. The primary endpoint is the “change in the surgical conduct” (CSC), i.e., the need to perform further dissection after intraoperative NIR/ICG technology activation at the end of D2 lymphadenectomy. Secondary endpoints include the pattern of abdominal fluorescence distribution according to tumor and patient characteristics, the preoperative clinical variables potentially associated with CSC, and the incidence of stage migration due to NIR/ICG application.

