### Statistical Analysis

A biostatistician (DG) will perform the statistical analysis. Continuous variables are described as mean (standard deviation) or median (interquartile range) according to distribution; categorical variables are reported as frequency (percentage). Normal distribution of continuous variables is assessed with the Kolmogorov–Smirnov test. Continuous variables are analyzed using Student’s *t*-test or Mann–Whitney test and categorical variables analyzed using Fisher’s exact test or chi-square test as appropriate. All statistical tests are two-sided and a level of <0.05 is used to indicate statistical significance. CSC will be modeled *via* a generalized linear model in the binomial family. The identification of preoperative variables independently associated with CSC will be performed by stepwise selection and using Akaike information criterion (AIC) as benchmark for inclusion. Goodness of fit will be based on the Somers’ Dxy index, adjusted for optimism in accuracy *via* bootstrap resampling (35). A graphic representation of the patterns of fluorescence distribution in the abdominal regions will be represented. Statistical analysis is conducted in R (R Core Team, 2020) (33).

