### Step 2: Intraoperative Application of NIR/ICG Technology (First Time)

Surgical intervention is performed exclusively *via* a minimally invasive approach, either laparoscopic or robotic, at the most 20 h after endoscopic submucosal ICG injection.

Intraoperative application of NIR/ICG technology is accomplished by using special optical devices adapted to fluorescence imaging. Using high-resolution video cameras linked to the ICG surgical endoscope, the technology allows a real-time ICG-enhanced visualization of LNs by toggling seamlessly between white light (which means light in the range of the spectrum visible by the normal human eye, 400–700 nm) and ICG fluorescence mode (NIR wavelength, 800–1,000 nm) in an “overlay way.”

A brief visualization of the operative field with NIR/ICG technology is performed in two moments at the beginning of surgery, during the exploration of the abdominal cavity and after the colo-epiploic detachment, in order to assess the presence of fluorescence in the following perigastric and locoregional sites:

- Lesser gastric curvature (no. 1, 3 nodal stations)- Greater gastric curvature (no. 2, 4 nodal stations)- Suprapyloric and hepatoduodenal ligament region (no. 5, 8, 12 nodal stations)- Gastropancreatic fold (no. 7, 9, 11 nodal stations)- Duodenopancreatic region (no. 6 nodal stations)- Tail of the pancreas and splenic hilum region (in the case of total gastrectomy, no. 11 and 10 nodal stations)

ICG-absorbing sites appearing as green spots and emitting fluorescence are defined as fluorescent sites.

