### Step 4: Intraoperative Application of NIR/ICG Technology (Second Time) and Definition of CSC

At the end of D2 lymphadenectomy “with the naked eye,” a visualization of the operative field is performed using NIR/ICG technology in order to verify the presence of residual LN in each D2 nodal station.

The CSC is defined in the case of persistence of fluorescence in one or more D2 nodal stations after the completion of D2 lymphadenectomy performed with the “naked eye,” requiring further dissection to remove the residual D2 nodal fluorescent structures.

The nodal stations dissected after NIR/ICG visualization are also recorded.

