## Study Limitations

The iGreenGO Study presents several potential limitations: first of all, the time interval for ICG injection is wide, potentially generating heterogeneity in the methods between participating centers. However, the ideal time for ICG injection is not universally established and a wide time interval is necessary in order to encounter clinical practice and organizational aspects of all participating centers. In addition, in the case of stenotic cancers, ICG injection can be performed at four proximal tumor points. In this case, the injections and the lymph nodes seen may not be representative of all the lymphatic drainage pathways. However, specific subgroup analyses were performed in order to mitigate this possible bias.

Lastly, the sequence for D2 nodal station dissection is not standardized and it is left to the preference of each participating center. However, the pictures taken after lymphadenectomy and the sole inclusion of centers that have performed at least 20 gastrectomies *via* a minimally invasive approach before participating in the study aim to offset these differences. Furthermore, the inclusion of different surgical approaches (laparoscopic and robotic) should increase the reproducibility of the results.

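### Injection-to-surgery time varies by centre but is not guaranteed a place in the fluorescence-pattern or CSC-predictor analyses, and the latest permitted injection is worded in two ways

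*Protocol article*

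**What the plan says.** **Injection window.** Protocol article, Step 1: "Patients undergo upper GI endoscopy at any time between 20 h before and the initiation (skin incision) of the planned surgery". The Abstract (Methods) gives the same outer limit, "submucosal peritumoral ICG injection at the most 20 h before surgery", and then adds: "Intraoperative endoscopic injection before starting surgical dissection is also allowed". Step 2 repeats only the outer limit: surgery takes place "at the most 20 h after endoscopic submucosal ICG injection".

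**When fluorescence is read.** Both readings are tied to operative events, not to time since injection. The first, which maps the fluorescent sites, is in Step 2: "A brief visualization of the operative field with NIR/ICG technology is performed in two moments at the beginning of surgery", namely at exploration and again after colo-epiploic detachment. The second, which determines CSC, follows the white-light D2 dissection (Step 4): "a visualization of the operative field is performed using NIR/ICG technology in order to verify the presence of residual LN in each D2 nodal station".

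**What is analysed.** Under Endpoints, the pattern is related to tumour and patient characteristics, and CSC to preoperative clinical variables. Under Statistical Analysis: "The identification of preoperative variables independently associated with CSC will be performed by stepwise selection", with AIC as the criterion. No term for injection time or for centre is named.

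**What is conceded.** Study Limitations: "the time interval for ICG injection is wide, potentially generating heterogeneity in the methods between participating centers". The reasons given are that no ideal time is established and that centres are organised differently.

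**The concern.** The Background explains that ICG binds interstitial proteins, enters lymphatic vessels and is taken up by nodes along the drainage path. What fluoresces at a given look can therefore depend on how long the tracer has had to travel. Two patients with the same tumour could give different maps because one was injected the day before and the other in theatre.

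Two secondary objectives are exposed.

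- **Pattern.** A site that is dark because tracer has not arrived cannot be told from a site that does not drain the tumour, unless the analysis takes timing into account.
- **CSC predictors.** By the article's own account timing follows the centre. If patients also differ between centres, a patient factor can pick up a timing effect. A stepwise rule may drop timing even where it is a candidate.

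**Working it through.** **1. Latest injection time, side by side.** Step 1 closes the window at skin incision. The Abstract closes it at the start of dissection. An injection in theatre before incision satisfies both. An injection after incision but before dissection satisfies the Abstract and breaches Step 1. The disagreement is confined to that short interval.

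**2. Spread of elapsed time.**
- First look: from shortly after injection (injection at or near incision) to about 20 h plus the time to exploration and colo-epiploic detachment.
- Second look: the same plus the dissection time. Its lower end is therefore the length of the operation up to that point, not near zero. The documents give no operating time.

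**3. Effect on the sample size.** Table 1 uses the Wilson interval: the smallest n with z·√n/(n+z²)·√(p(1−p)+z²/(4n)) ≤ d, where z = 1.96. At p = 17% this gives 338, 267 and 216 for d = 4%, 4.5% and 5%, against 337, 266 and 217 printed. The table reproduces to within one patient in these cells, and the present point does not touch it. Expected CSC events are 0.17 × 217 = 36.9 to 0.17 × 337 = 57.3.

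**4. Effect on the primary proportion.** CSC incidence is a single-arm proportion, so there is no comparison for timing to confound. With share w injected early, the estimate is w·p(early) + (1−w)·p(late), an average over whatever mix the centres produce.

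**5. Effect on a predictor (all timing inputs assumed).** Take a factor with no effect of its own. Let timing change CSC from *lo* to *hi*, and let shares *a* and *b* of the patients with and without the factor have the *hi* timing. Then p₁ = a·hi + (1−a)·lo and p₀ = b·hi + (1−b)·lo.

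Worked case, lo = 12%, hi = 22%, a = 0.6, b = 0.4:
- p₁ = 0.6 × 22% + 0.4 × 12% = 18%
- p₀ = 0.4 × 22% + 0.6 × 12% = 16%
- OR = (0.18/0.82)/(0.16/0.84) = 1.15

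Chance of p < 0.05 with N = 337 split equally: SE = √[(0.18×0.82 + 0.16×0.84)/168.5] = 0.0409 and 0.02/SE = 0.49. The two-sided probability is about 8%, against 5% if there were no distortion.

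| lo / hi | a / b | p₁ / p₀ | spurious OR | chance of p < 0.05 |
|---|---|---|---|---|
| 12 / 22% | 50 / 50% | 17.0 / 17.0% | 1.00 | 5% |
| 14 / 20% | 65 / 35% | 17.9 / 16.1% | 1.14 | 7% |
| 12 / 22% | 60 / 40% | 18.0 / 16.0% | 1.15 | 8% |
| 12 / 22% | 80 / 20% | 20.0 / 14.0% | 1.54 | 31% |
| 10 / 24% | 80 / 20% | 21.2 / 12.8% | 1.83 | 54% |

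With timing balanced over the factor there is no distortion. A large effect needs both a strong timing effect and a strong imbalance.

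**The case against.** The other side has good arguments.

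- **It may be covered elsewhere.** The article lists no candidate covariates. Timing of an injection given before incision could count as a preoperative variable, and case-report fields and covariate lists commonly sit in the full protocol or analysis plan. This stands against any claim that timing is unrecorded or excluded. It does not answer that the stated rule lets stepwise selection remove timing, or that the pattern endpoint is framed without it.
- **It is disclosed and justified.** The wide interval is the first limitation named, with reasons, in an observational study. That supports leaving the window wide. It is not an analytic safeguard. The subgroup analyses mentioned in that section come directly after the point about stenotic tumours, are not defined, and do not appear under Statistical Analysis.
- **The wording conflict is narrow.** This stands. Intraoperative in the Abstract may simply mean in theatre before incision.
- **The causal chain is incomplete.** This stands in part. No migration time is given, and no passage says that centres differ in case mix.

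A reader might go further and infer that the primary CSC result is biased, or that neither secondary objective can be answered. The documents do not support either. The primary proportion involves no comparison, and predictor bias needs two associations whose size is not given.

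**Conclusion.** The point holds as one of analysis and wording. Injection timing is an acknowledged, centre-driven source of heterogeneity, and the stated pattern and CSC-predictor analyses do not guarantee it a place. Step 1 and the Abstract need reconciling on the latest injection.

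The primary CSC proportion and Table 1 are unaffected, except that the proportion describes a mix of timings. For the predictors, distortion is conditional: small under moderate assumptions (odds ratio about 1.15) and material only under strong ones (1.54 to 1.83 with an 80/20 imbalance). For the pattern analysis the route is more direct, because elapsed time can alter the map itself, but the documents give nothing from which to size it. Every timing effect and imbalance used here is an assumption. The change is worth making because it is cheap, not because serious bias has been shown.

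**What to change.** 1. Reconcile Step 1 and the Abstract on whether injection after skin incision is permitted. No window is proposed here.
2. Take injection and incision times from endoscopy and theatre records. Enrolment began in September 2021, so recover them for patients already included.
3. Force injection-to-incision time into the CSC model, exempt from stepwise removal, either as a continuous term or as day-before / same-day / intraoperative. If injection after incision is permitted, the continuous form takes negative values for those patients; the categories avoid this.
4. Account for centre, for example by a random intercept or cluster-robust standard errors.
5. Report the fluorescence pattern by injection-timing category, using the same look or looks for every patient, so that the pattern is not defined differently by timing group.
6. Do not use injection-to-second-look time as the covariate. It contains dissection time, which preoperative factors may affect, so adjusting for it could remove part of the associations sought.

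**Cost.** One degree of freedom if continuous, two with three categories, against roughly 37 to 57 expected events. Patient care does not change. The main drawback is collinearity: where a centre always injects at the same time, timing and centre effects cannot be fully separated, and the report should say so.

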### Step 2: Intraoperative Application of NIR/ICG Technology (First Time)

Surgical intervention is performed exclusively *via* a minimally invasive approach, either laparoscopic or robotic, at the most 20 h after endoscopic submucosal ICG injection.

Intraoperative application of NIR/ICG technology is accomplished by using special optical devices adapted to fluorescence imaging. Using high-resolution video cameras linked to the ICG surgical endoscope, the technology allows a real-time ICG-enhanced visualization of LNs by toggling seamlessly between white light (which means light in the range of the spectrum visible by the normal human eye, 400–700 nm) and ICG fluorescence mode (NIR wavelength, 800–1,000 nm) in an “overlay way.”

A brief visualization of the operative field with NIR/ICG technology is performed in two moments at the beginning of surgery, during the exploration of the abdominal cavity and after the colo-epiploic detachment, in order to assess the presence of fluorescence in the following perigastric and locoregional sites:

- Lesser gastric curvature (no. 1, 3 nodal stations)- Greater gastric curvature (no. 2, 4 nodal stations)- Suprapyloric and hepatoduodenal ligament region (no. 5, 8, 12 nodal stations)- Gastropancreatic fold (no. 7, 9, 11 nodal stations)- Duodenopancreatic region (no. 6 nodal stations)- Tail of the pancreas and splenic hilum region (in the case of total gastrectomy, no. 11 and 10 nodal stations)

ICG-absorbing sites appearing as green spots and emitting fluorescence are defined as fluorescent sites.

### Step 3: Surgical Intervention and Lymphadenectomy

The type of surgical resection is assessed according to the tumor site and is accomplished according to JGCA guidelines (9).

More specifically:

- Distal gastrectomy (DG) with D2 lymphadenectomy includes the resection of two-thirds of the stomach including the pylorus and dissection of 1, 3, 4sb, 4sd, 5, 6, 7, 8a, 9, 11p, and 12a lymph node stations.- Total gastrectomy (TG) with D2 lymphadenectomy includes the total resection of the stomach including the cardia and pylorus and dissection of 1, 2, 3, 4sa, 4sb, 4d, 5, 6, 7, 8a, 9, 11p, 11d, and 12a lymph node stations.

Digestive tract reconstruction can be accomplished *via* a mini-laparotomy through an abdominal incision not greater than 10 cm. Any abdominal incision greater than 10 cm will be classified as a conversion to open approach, as well as any need to complete the resection phase by any type of laparotomy. A specific sequence of D2 nodal station dissection is not mandatory; the D2 lymphadenectomy technique described by Giacopuzzi et al., which is based on the takeover of specific vascular landmarks, is used in most participating centers (37).

Surgical resection with D2 lymphadenectomy is performed “with the naked eye,” which means using conventional white-light imaging visualization without application of NIR/ICG technology.

### Step 4: Intraoperative Application of NIR/ICG Technology (Second Time) and Definition of CSC

At the end of D2 lymphadenectomy “with the naked eye,” a visualization of the operative field is performed using NIR/ICG technology in order to verify the presence of residual LN in each D2 nodal station.

The CSC is defined in the case of persistence of fluorescence in one or more D2 nodal stations after the completion of D2 lymphadenectomy performed with the “naked eye,” requiring further dissection to remove the residual D2 nodal fluorescent structures.

The nodal stations dissected after NIR/ICG visualization are also recorded.

### Postoperative Management

Postoperative care is accomplished according to the standard practice of each surgical participating institution. Epidural analgesia, early mobilization, and enteral feeding are recommended according to ERAS guidelines (38). Discharge criteria include the absence of fever, effective analgesic oral therapy, mobilization and self-management at least similar to preoperative status, and oral and/or enteral nutrition able to provide at least 60% of the daily energy requirement.

### Pathology

Surgical specimens are processed and analyzed by the pathology department of each participating institution following national and international guidelines (4).

The tissue sample is routinely fixed in 10% neutral formalin and embedded in paraffin. Commercially available monoclonal antibodies such as immunohistochemical stains for CK AE1/AE3 (Dako Omnis^®^) are performed where appropriate. One dedicated pathologist per institution examines the relative resected specimens. Pathologic reports are drawn up reporting morphological subtypes according to Lauren (39) and the WHO Classification of Tumors (40). In the case of NACT, histopathological tumor regression grade is assessed according to Becker’s grading system (41). Further histopathological variables include tumor size, Borrmann classification (42), grade of differentiation, margin status, presence of lymphovascular (LVI) and perineural (PNI) invasion, and lymph node ratio (LNR), expressed as the ratio between positive LNs and the total number of retrieved LNs.

In microscopic vision, an LN is defined as a delimited area of lymphoid cells containing a follicular architecture, with or without a subcapsular sinus. Tumoral cells containing LNs are defined as metastatic. The additional LNs retrieved while using the NIR/ICG technology are signaled to the pathologist by the operating surgeons. Surgical specimens are assessed in order to obtain a final pathologic report, expressed as pTNM/ypTNM, according to the eighth edition of the AJCC Staging System (10).

### Follow-Up

Postoperative follow-up and long-term surveillance are achieved through physical examination, blood test analysis, esophagogastroduodenoscopy (EGDS), and CT scan in accordance with national and international recommendations (43, 44).

### Surgical Quality Control

Participating centers are academic and non-academic hospitals with a history of at least 20 gastrectomies performed *via* a minimally invasive approach. Photographs of the surgical field are taken at the end of nodal dissection before NIR/ICG fluorescence technology activation and sent to the coordinating center. The criteria suggested by Giacopuzzi et al. (37) are used in order to assess the completeness of lymphadenectomy performed with the “naked eye.” These inclusion criteria aim to ensure high-quality standards of surgery.

## Discussion

Despite encouraging results from Eastern countries, the prognosis of gastric cancer in Western population remains poor (1, 2). Both tumor and patient features, such as a more aggressive biological behavior, an advanced stage at diagnosis, an older age, a higher BMI, and the presence of multiple comorbidities, contribute to this dismal prognosis (20).

Surgery remains the best treatment option for patients with resectable gastric cancer (4). Several efforts have been made to safely extend surgical indications beyond traditional limits, such as the introduction of conversion surgery in stage IV gastric cancer as proposed by Yoshida et al. (45), and to improve the quality of surgery by using novel imaging devices. The introduction of NIR/ICG technology in the surgical treatment of AGC has gained growing attention, and several studies suggesting its potential advantage have been published (24, 25). However, several questions regarding NIR/ICG technology application remain unanswered and its actual clinical value is still a matter of debate.

Since ICG allows us to easily distinguish lymphatic vessels and LNs from the surrounding fatty tissue and vascular structures (14), the intraoperative application of NIR/ICG technology might help surgeons to improve lymphadenectomy (21, 25, 27). In the RCT by Chen et al., when residual LNs containing fluorescence were detected in the dissected area, a complementary dissection was performed; moreover, if fluorescent LNs were detected outside the planned dissection area, further dissection beyond D2 lymphadenectomy was performed, configuring *de facto* a D2+ lymphadenectomy. The authors reported a significantly higher mean number of retrieved LNs in the ICG group as compared with the non-ICG group (mean 50.5 vs. 42.0, *p* < 0.001) (27). Of note, current evidence does not support the routine adoption of D2+ lymphadenectomy except for selected cases (4, 9, 46).

On the contrary, Lan et al. reported no significant difference in the number of retrieved LNs among patients who underwent robotic gastrectomy with or without NIR/ICG technology application (23). Although binding to interstitial proteins (albumin, globulins, etc.) and spreading in the lymphatic vessels, ICG has a twofold limit. Firstly, it has a low sensitivity for metastatic LNs (reported 56.3%) and should not therefore be considered a metastatic nodal tracer (27). In addition, it is not specific for LNs because soft tissues without LNs can be occasionally stained with ICG (25).

For these reasons, although lymphadenectomy is one of the main steps in curative-intent surgery for gastric cancer and nodal status is the most important prognostic factor for survival, whether the overall number of harvested LNs should be considered the best indicator of the NIR/ICG technology clinical value remains a matter of debate.

With the present study protocol, we address this issue from a different perspective, evaluating whether the application to NIR/ICG technology can lead to a CSC. Moreover, the incidence of CSC is evaluated in a cohort of patients undergoing surgical intervention with D2 lymphadenectomy performed by expert surgeons in Western hospitals.

